#### Secondary outcomes

Length of hospitalization: The length of hospitalization will be recorded during the treatment.Overall Survival: Survival time up to 16 weeks.Acute exacerbation rate: The number of participants with AE-IPF will be recorded during the follow-up period.Intubation rate: The number of participants with intubation will be recorded throughout the study period.Dyspnea: The Modified British Medical Research Council (mMRC) questionnaire [21] was used to assess dyspnea, as the mMRC reflects breathlessness in patients with IPF, and it could be used as a simple screening tool for efficacy assessment [22]. It will be completed and recorded at baseline, 7 days, 2 weeks, 4 weeks (end of the treatment), and 16 weeks (end of the follow-up). The mean change of the mMRC score between baseline to 4 weeks and 16 weeks will be statistically analyzed.Quality of life: The IPF-specific version of the St George’s Respiratory Questionnaire for idiopathic pulmonary fibrosis (SGRQ-I) will be adopted to assess the health-related quality of life (HRQL) of patients with AE-IPF. The SGRQ-I was developed based on patients with IPF [23, 24]. It will be completed and recorded at baseline, 7 days, 2 weeks, 4 weeks (end of the treatment), and16 weeks (end of the follow-up). The mean change of the SGRQ-I total score between baseline to 4 weeks and 16 weeks will be statistically analyzed.The partial pressure of oxygen (PaO_2_) and oxygen index: Arterial blood gas analysis will be tested and recorded at baseline, 7 days, and 2 weeks.

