## Background

Idiopathic pulmonary fibrosis (IPF) is a chronic, progressive, fibrotic lung disease of unknown etiology occurring in adults [1]. It is characterized by worsening lung function and leading to respiratory failure and death [2]. Post-diagnosis median survival of patients with IPF has been reported to range from 2 to 3 years [1, 3–6]. However, some IPF patients have experienced a rapid progression of respiratory failure, which is called acute exacerbation of IPF (AE-IPF). AE-IPF is one of the leading causes of deterioration and mortality of patients with IPF [7–9]. AE-IPF can occur at any stage of IPF, with a dangerous condition, rapid progress, high mortality, and poor prognosis. The incidence of AE-IPF reported in the literature was significantly different due to the lack of a unified diagnostic standard, research methods, and different populations. The annual incidence of IPF has recently been estimated at 5~10% in the official Clinical Practice Guideline [1]. In many prospective studies, the annual incidence rate was slightly higher than 20% [10–12]. According to reports, the median survival period is about 3–4 months, and the mortality rate during hospitalization after acute exacerbation is 55–80% [1, 11, 13]. Nearly 90% of patients with AE-IPF need to be treated in ICU [14], and those who survive after the first acute exacerbation have a mortality rate of more than 90% after 6 months [15]. Therefore, the prevention, early diagnosis, and active treatment of AE-IPF are the primary and arduous medical tasks in clinical practice. It is particularly important to carry out therapeutic research on AE-IPF.

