### Statistical analysis

The statistical analysis in this trial will be performed by Jiangsu Famous Medical Technology Co., Ltd. in Nanjing, China. The analysis will be based on the full analysis set, which is performed based on the ITT population.

In the descriptive data, continuous variables are described as mean (SD) and standard deviation or median and interquartile, categorical variables are described as numbers and percentages. The primary outcome of this study is treatment failure rate and all-cause mortality rate in each group. They will be compared between groups using the *χ*^2^ test or Fisher’s exact test. In secondary outcome analysis, the mMRC score for dyspnea, the SGRQ-I score for quality of life, the PaO_2_, and oxygen index will be used to analyze the difference, and differences between groups in mean change between baseline and measurements made at each time point will be analyzed by analysis of covariance. The length of hospitalization will be compared using the independent Student’s *t*-test or the Wilcoxon rank-sum test according to the normality of the data. Overall Survival, acute exacerbation rate, and intubation rate will be compared between groups using the *χ*^2^ test or Fisher’s exact test. The two groups will be compared using the 95% confidence interval method to determine superiority. SAS®, Version 9.2, performed all statistical analyses.

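### Length of hospitalization is compared with no provision for in-hospital death, so an arm with more early deaths can show a shorter stay

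*Protocol article*

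**What the plan says.** Under Secondary outcomes, the protocol article states: "Length of hospitalization: The length of hospitalization will be recorded during the treatment". Treatment lasts 4 weeks, and Table 1 records this outcome at day 7, week 2 and week 4. Under Statistical analysis, "The length of hospitalization will be compared using the independent" Student's t-test "or the Wilcoxon rank-sum test according to the normality of the data". The same section bases the analysis on the full analysis set, derived from the intention-to-treat population.

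The Background reports that "the mortality rate during hospitalization after acute exacerbation is 55–80" per cent and puts median survival at about 3–4 months. Death is a component of treatment failure and is the whole of all-cause mortality, both primary; it also enters overall survival. No section says what death does to length of hospitalization. The Participants section mentions intention to treat as a way of handling data missing through dropout, but a death that ends a stay is not a dropout.

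Two other secondary outcomes are simple counts. For exacerbation, "The number of participants with AE-IPF will be recorded during the follow-up period", which Table 1 places at weeks 8, 12 and 16. For intubation, "The number of participants with intubation will be recorded throughout the study period". Both go to a chi-square or Fisher's exact test: "Overall Survival, acute exacerbation rate, and intubation rate will be compared between groups using the" one or the other. No denominator is given for either rate.

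**The concern.** A hospital stay can end in discharge alive, which is good, or in death, which is the worst result. A t-test or Wilcoxon test on the raw number of days cannot tell them apart: a patient who dies on day 3 and one who goes home on day 3 both score 3. Patients still in hospital at week 4 are cut off there and treated as if their stay were complete. If the arms differ in early mortality, the comparison mixes that difference with any difference in recovery and gives it the wrong sign.

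This would be a detail in a population where few die in hospital. Here the article's own Background suggests that death could end a large share of stays. The Sample size section says the results will feed the sample size calculation of a further study, so a distorted estimate could be carried forward.

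Exacerbation and intubation raise a related question. If the crude count is divided by all randomised patients, someone who dies before having the event counts as event-free.

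**Working it through.** The plan gives no figure for length of hospitalization, so there is none to reproduce. The check is whether the analysis as written can point the wrong way, and by how much.

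**Inputs.** From the article: 40 patients per arm; a 28-day window; t-test or Wilcoxon. Assumed: constant hazards of discharge alive (x) and of death in hospital (d), death closes the stay, two-sided 5% level. Arm A has x = 0.03 and d = 0.02 per day. Arm B has x = 0.03 and d = 0.04. Recovery is thus the same and only mortality differs. Let λ = x + d.

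**In-hospital death by day 28** = (d/λ)(1 − e^(−28λ)).
- A: (0.02/0.05)(1 − e^(−1.40)) = 0.40 × 0.753 = 30%
- B: (0.04/0.07)(1 − e^(−1.96)) = 0.571 × 0.859 = 49%

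**Mean stay, cut off at day 28** = (1 − e^(−28λ))/λ.
- A: 0.753/0.05 = 15.1 days
- B: 0.859/0.07 = 12.3 days

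The arm with more deaths looks 2.8 days better. In 4,000 simulated trials, Wilcoxon gave p<0.05 in its favour in about 23%, and in the other direction in under 0.1%.

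**Other mortality levels** (discharge hazard equal in the arms, 1/40 or 1/20 per day; 4,000 trials each):

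| In-hospital mortality | Mean stay, hazard 1/40 | Mean stay, hazard 1/20 | Wilcoxon favours the high-mortality arm |
|---|---|---|---|
| 30% v 50% | 16.2 v 13.1 days | 11.6 v 9.0 days | 24–26% |
| 55% v 65% | 12.3 v 10.5 days | 8.2 v 6.7 days | 13% |
| 55% v 80% | 12.3 v 7.1 days | 8.2 v 4.0 days | 72–83% |

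The last row uses the two ends of the Background's range as the two arms, which is an extreme contrast.

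**Dependence on the discharge hazard.** Let arm A also discharge faster: x = 0.05, d = 0.02. Arm B stays at x = 0.03, d = 0.04. Then λ = 0.07 in both arms and mean stay is 12.3 days in both. The sign no longer reverses, but a benefit on both discharge and survival disappears from view.

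**Does the replacement restore the direction?** In the first scenario:
- Discharged alive by day 28 = (x/λ)(1 − e^(−28λ)). A: 0.60 × 0.753 = 45%. B: 0.429 × 0.859 = 37%.
- Mean days alive and out of hospital, with in-hospital death scoring 0 and no death or readmission after discharge = x[28/λ − (1 − e^(−28λ))/λ²]. A: 0.03 × (560 − 301.4) = 7.8. B: 0.03 × (400 − 175.3) = 6.7.

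Both now favour the arm with fewer deaths. In 4,000 simulated trials, Wilcoxon on days alive and out of hospital was significant for the lower-mortality arm in about 8% and for the other in about 0.5%. The false direction is almost gone, but power is low.

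**Exacerbation, if the denominator is all randomised.** Assume a 30% risk in every week-4 survivor and early death of 20% v 40%. Recorded rates are 0.30 × 0.80 = 24% v 0.30 × 0.60 = 18%. If the denominator is those entering follow-up, the rates are 30% v 30%.

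**Intubation, same denominator.** Assume an intubation hazard of 0.01/day in both arms and a hazard of death without intubation of 0.01 v 0.03/day. Over 112 days:
- (0.01/0.02)(1 − e^(−2.24)) = 44.7%
- (0.01/0.04)(1 − e^(−4.48)) = 24.7%

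These formulas are the cumulative incidence with death competing. With complete follow-up that equals the crude proportion, so a competing-risk analysis of these two outcomes would return the same figures.

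**The case against.** The strongest reply is that the article is a condensed text, that it nowhere says death counts as discharge, and that an unseen analysis plan may hold a rule. That stands in part: the fault is that no provision is stated, not that the authors chose to ignore death. But the article does fix the variable, window, test and analysis set. Followed as written, that combination scores early death as a short stay.

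The mortality figure is also open to challenge. It comes from the literature, in a Background that says nearly 90% of patients need intensive care. The exclusion criteria remove invasive ventilation, unstable haemodynamics, NYHA class IV heart failure and bedridden patients. Mortality here may be lower, and the article does not estimate it. The 30% v 49% scenario lies below the cited range and the problem remains.

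A reader might infer more: that a harmful treatment will always shorten stay, or that length of hospitalization, exacerbation and intubation all become uninterpretable. The documents do not support this. The reversal of sign rests on equal discharge hazards and vanishes in the example with faster discharge. The direction for exacerbation rests on a denominator the article does not state; an analysis of survivors only would carry selection of uncertain direction. For intubation, only death without intubation matters. Treatment failure already combines intubation, ventilator treatment and death over 4 weeks, and over 16 weeks intubation-or-death would overlap heavily with all-cause mortality.

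Finally, mortality is reported beside these outcomes as a primary endpoint, so a difference large enough to distort stay would be examined directly. That limits the harm but does not make the stay comparison itself meaningful.

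**Conclusion.** The point holds for length of hospitalization, at modest severity. As stated, the analysis can show a shorter stay in the arm with more early deaths: 2.8 days shorter, and significant by Wilcoxon in about 23% of trials, when in-hospital death is 30% v 49% and discharge hazards are equal. This assumes that death closes the stay and that those who die remain in the analysis, the natural reading of an intention-to-treat set. The hazards are assumptions, so the sizes are illustrative.

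For exacerbation and intubation the point is secondary and conditional: it applies if the crude proportions are taken over all randomised patients. Neither primary outcome is affected, and the trial is exploratory.

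**What to change.** Replace the comparison of raw stay with one of these:
- Days alive and out of hospital to day 28, with in-hospital deaths scoring 0, compared by Wilcoxon.
- Time to discharge alive, with death as a competing event, compared by Gray's test and censored at day 28. This works here because discharge is the favourable event, so deaths lower its cumulative incidence.

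Describe raw stay only among patients discharged alive, without a test.

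For exacerbation and intubation, state the denominator and report event-or-death beside the crude rates. Cumulative incidence with death competing should not be offered as the correction.

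The cost is mainly analysis wording, since the trial already records stay and death. Two downsides should be accepted openly: the outcome is no longer a plain number of days in hospital, and some power is lost. One check is needed first. The section on withdrawal, dropout and discontinuation lists deterioration and serious adverse events, and the article does not say whether discharge, intubation and exacerbation are still recorded afterwards. The replacement needs those data for every randomised patient.

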### Safety assessment

Any adverse event will be recorded for evaluating the safety of the Kangxianhuanji granule. Besides, routine blood tests, liver and kidney function, and electrocardiograph examinations will be performed before and after the treatment will be used to assess safety.

Any adverse event will be recorded in time, and the results of the causal assessment will be recorded. If a severe adverse event occurs in the study, it will be reported to the project manager and the Ethics Committee immediately. They will decide on whether to continue or stop the study. All adverse events should be tracked until properly resolved or stabilized.

After the study, the subjects should continue to be given necessary health guidance to tell them that they will still be concerned and will be followed up regularly. The researcher shall keep in touch with the subjects, instruct them to take medicine on time, and understand their diet, activities, rest, and medication. Timely give corresponding psychological counseling according to the subject's condition and psychological changes. In case of any change of condition, contact the doctor or go to the hospital for diagnosis and treatment in time.

### Data management and monitoring

Data collected in this trial will be derived from case report forms (CRFs). Any information about the primary and secondary outcomes at each timeline of the study will be recorded in the CRFs by the outcome assessors. The study monitors will be responsible for checking the integrity and quality of the completed CRFs. Two independent data administrators will be responsible for recording data on the Data Management System, which designed and built by Jiangsu Famous Medical Technology Co., Ltd. in Nanjing, China. The personal information of the participants will be protected, and the database can only be accessed with the permission of the research leader unit.

This trial refers to the universal standard of clinical trial audit [25], and the inspection mainly includes clinical trial project inspection and quality and risk management. The audit of the clinical trial project focuses on the authenticity and integrity of research data and is carried out in the preparation stage, the progress stage, and the conclusion stage of the clinical trial, respectively.

During the study, the following measures were taken to ensure the confidentiality and security of the subjects’ personal information. First, create a code to replace the recognizable information of the subject with an irrelevant character sequence. Secondly, use encrypted files and storage media that need to input passwords to ensure the maintenance and link of data in different systems. Third, limit the number of people who can carry out quality control, inspection, and analysis.

### Statistical analysis

The statistical analysis in this trial will be performed by Jiangsu Famous Medical Technology Co., Ltd. in Nanjing, China. The analysis will be based on the full analysis set, which is performed based on the ITT population.

In the descriptive data, continuous variables are described as mean (SD) and standard deviation or median and interquartile, categorical variables are described as numbers and percentages. The primary outcome of this study is treatment failure rate and all-cause mortality rate in each group. They will be compared between groups using the *χ*^2^ test or Fisher’s exact test. In secondary outcome analysis, the mMRC score for dyspnea, the SGRQ-I score for quality of life, the PaO_2_, and oxygen index will be used to analyze the difference, and differences between groups in mean change between baseline and measurements made at each time point will be analyzed by analysis of covariance. The length of hospitalization will be compared using the independent Student’s *t*-test or the Wilcoxon rank-sum test according to the normality of the data. Overall Survival, acute exacerbation rate, and intubation rate will be compared between groups using the *χ*^2^ test or Fisher’s exact test. The two groups will be compared using the 95% confidence interval method to determine superiority. SAS®, Version 9.2, performed all statistical analyses.

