### Sample size

It is the first exploratory study to explore the efficacy of TCM in patients with AE-IPF. At present, we have not found the research data of AE-IPF treated by TCM, and the formal sample size calculation is not possible. We referred to the calculation method of the minimum sample size in exploratory clinical research, 40 participants in the intervention group, and 40 in the control group (*N* = 80 in total). The result of this study will provide data for a formal sample size calculation for further study.

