### Randomization and blinding

The multicenter, dynamic, blocked randomization method is adopted. An independent statistician will produce the random allocation sequence via the PLAN sentences of the Strategic Applications Software (SAS®) Version 9.2 (KEY: FQ37-WSB8-7G5C). After signing the informed consent, the eligible participants will be allocated randomly into either the intervention group or control group at a 1:1 ratio using the SAS9.2 software with a block size of 4. The scheme of random allocation will be obtained from a central stochastic distribution system provided by Jiangsu Famous Medical Technology Co., Ltd. in Nanjing, China.

Except for those responsible for blinding, all participants and investigators will be blinded to the group. The odor and color of Kangxianhuanji granule and placebo look the same, and the packaging is the same. The group’s distribution will not be disclosed unless the researchers had to know the details of the medication being taken by a participant. The study blind will be broken after all participants have finished the study. In case of emergency (such as serious adverse events, or suspected unexpected serious adverse reactions), or when the participant needs to be rescued and must know what kind of treatment the patient has received, the study blind will be opened after consultation of the administrator of research organization.

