There are some limitations to this study. First, there is no proven, effective treatment for AE-IPF at present. High-dose corticosteroids and antibiotics are widely used, but the dose of appropriate and duration therapy remains unclear. It will result in a very different primary treatment for each participant. Another limitation is that due to the lack of preliminary evidence-based studies, the sample size estimated by exploratory research is too small, and the follow-up time is short. The results and conclusions will be limited. However, based on the result obtained from this study, a clinical trial with a long follow-up period and a large sample size will be conducted.

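### Both primary outcomes get an unadjusted chi-square or Fisher test although oxygenation is measured at baseline; the test is valid but may give up precision in an 80-patient trial

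*Protocol article*

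**What the plan says.** In the Protocol article, Statistical analysis: "The primary outcome of this study is treatment failure rate and all-cause mortality rate in each group". The next sentence fixes the method: "They will be compared between groups using the" chi-square test or Fisher's exact test. No covariate or centre term is named. The same section treats mMRC, SGRQ-I, PaO2 and oxygen index differently: "differences between groups in mean change between baseline and measurements made at each time point will be analyzed by analysis of covariance".

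The Secondary outcomes section states that "Arterial blood gas analysis will be tested and recorded at baseline, 7 days, and 2 weeks". Table 1 also marks blood gas analysis at the baseline visit. (Table 1 adds a week 4 measurement that the text omits; this does not affect the present point.)

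The Sample size section sets "40 participants in the intervention group, and 40 in the control group" without a formal calculation. On allocation, the Randomization and blinding section says "The multicenter, dynamic, blocked randomization method is adopted" and gives the ratio and block size as "at a 1:1 ratio using the SAS9.2 software with a block size of 4". It does not say whether allocation is stratified by centre.

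**The concern.** With two binary primary outcomes and 40 patients per arm, the comparison is imprecise from the start, and the limitations paragraph of the Discussion itself concedes that the sample is too small. The listed eligibility criteria set no oxygenation range, admit ages 40 to 80 and allow up to 7 days of earlier treatment, so severity at entry can vary widely. Treatment failure includes intubation, ventilator treatment and death, so baseline oxygenation is a plausible predictor of it.

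If it does predict outcome, a comparison that ignores it leaves explainable variation in the treatment estimate. The trial is also meant to supply data for a later sample size calculation, so a tighter estimate serves its stated purpose. The unadjusted test is written into the plan, so this is a choice made and not a detail left open.

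**Working it through.** **Inputs from the Protocol article.** 40 per arm, 1:1, blocks of 4. The Background section cites in-hospital mortality of 55 to 80%; that is context and not a design input. No power, effect size or alpha is given, so the 80 cannot be reproduced.

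**Assumptions.** Two-sided 0.05 (the plan uses 95% confidence intervals); control rates of 65% or 55%; one standardised baseline covariate whose prognostic strength is varied, because the article does not give it.

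**Step 1: chance imbalance.** The between-arm difference in a standardised baseline value has SD sqrt(2/40) = 0.224.
- P(at least 0.3 SD) = 2 × (1 − Φ(0.3/0.224)) = 0.18
- P(at least 0.2 SD) = 2 × (1 − Φ(0.2/0.224)) = 0.37

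**Step 2: unadjusted benchmark.** With a 65% control rate and 40 per arm, the usual two-proportion formula gives power of 27%, 43%, 61% and 78% for differences of 15, 20, 25 and 30 points. At 65% against 40%, the 95% CI half-width is 1.96 × sqrt((0.65 × 0.35 + 0.40 × 0.60)/40) = 0.212, or 21.2 points.

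**Step 3: gain from the covariate.** 2,500 simulated trials per scenario (N = 80, permuted blocks of 4) compared the chi-square test with a standardised risk difference from logistic regression on treatment and the covariate. The adjusted half-width is 21.2 × sqrt(variance ratio).

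| Assumed AUC (OR per SD) | Variance ratio, adjusted/unadjusted, 65 v 40 | Half-width (points) | Chi-square power, 65 v 40 | Adjusted power, 65 v 40 | Gain, 65 v 40 | Gain, 65 v 35 | Gain, 55 v 30 |
|---|---|---|---|---|---|---|---|
| 0.50 (1.0) | 1.017 | 21.4 | 64.5% | 63.4% | −1.1 | 0.0 | −0.1 |
| 0.64 (1.65) | 0.951 | 20.7 | 64.3% | 65.3% | +1.0 | +1.2 | +2.1 |
| 0.69 (2.12) | 0.902 | 20.1 | 65.5% | 68.6% | +3.1 | +2.8 | +4.6 |
| 0.74 (2.72) | 0.860 | 19.7 | 63.1% | 69.7% | +6.6 | +5.8 | +7.6 |
| 0.81 (4.48) | 0.749 | 18.3 | 64.7% | 78.6% | +13.9 | +10.3 | +14.6 |

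The simulation error of each power is about sqrt(0.65 × 0.35/2500) = 1 point. The simulated chi-square power (63 to 66%) sits slightly above the formula's 61%, so comparisons should be made within a row. Over all scenarios at AUC 0.69 to 0.81 the variance ratio runs from 0.91 to 0.72, so 80 adjusted patients are worth about 80/0.91 = 88 to 80/0.72 = 111 unadjusted ones.

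A separate simulation (1,500 trials per scenario, conditional log OR −1.3, likelihood-ratio test) points the same way: 77% against 80% at an OR of 2.0 per SD, 70% against 76% at 2.5, 64% against 72% at 3.0, and no gain at 1.5.

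**Step 4: type I error.** The standardised analysis rejected in 4.3 to 6.0% of null trials (simulation error about 0.4 points). The highest value, 6.0%, came with a non-prognostic covariate, where chi-square gave 5.3%.

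**Step 5: centre.** With four equal centres assumed, a Cochran-Mantel-Haenszel test by centre gained essentially nothing without centre differences, 0.2 points at a centre SD of 0.5 on the logit scale (80.8% to 81.0%), and 2.4 points at SD 1.0 (79.5% to 81.9%). At SD 1.0 the chi-square type I error was 4.0%, against 4.9% by centre: slightly conservative, not invalid.

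**The case against.** The strongest reply is that nothing here is an error. A chi-square or Fisher test of randomised arms holds its type I error, the trial is exploratory with no power target, and simple marginal rates feed directly into a later sample size calculation. The size of the gain rests on a prognostic strength that the article does not state, and it is negligible if that strength is low. All of this stands. It limits the point to efficiency but does not remove it: a standardised risk difference is also a marginal quantity, and the covariate is already collected.

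Some stronger readings are tempting but not supported:

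- **That chance imbalance biases the comparison or makes its interval too wide.** The imbalances in Step 1 are already covered by the unadjusted test's error rate and interval. An adjusted interval may be narrower; the unadjusted one is not wrong.
- **That ignoring centre and blocks is a material loss.** The article states neither stratification by centre nor the number of centres, and centre adds 0 to 2.4 points. Analysis by block would mean about 80/4 = 20 strata with two patients per arm in each, which is impractical. Adding four centre terms with no true effect gave likelihood-ratio type I error of 5.3 to 6.5%, a reason not to add them by default.
- **That analysis of covariance for the secondary outcomes shows inconsistency.** It is routine for change scores that have their own baseline; death and treatment failure have none.
- **That adjustment answers the Discussion's remark on background therapy, "It will result in a very different primary treatment for each participant".** That remark concerns corticosteroid and antibiotic dose and duration, which baseline oxygenation does not capture.
- **That the allocation wording undermines the primary test.** Whether a dynamic method fits a pre-generated SAS list in blocks of 4 is a separate question of wording; the term may describe central real-time assignment from that list.

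**Conclusion.** The point holds as a recommendation on efficiency, of modest weight in an exploratory trial. The planned primary tests are valid, but they may forgo precision that the baseline data could supply. For 65% against 40%, a covariate of moderate to fairly strong prognostic value narrows the 95% CI half-width by about 1 to 1.5 points, and a very strong one by about 3. The downside is small, since a non-prognostic covariate costs at most about one power point.

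The conclusion rests on assumed event rates, a single covariate and an assumed range of prognostic strength. No control rate for treatment failure is given, and the cited in-hospital mortality is not the 16-week rate. The gain should therefore be stated as a range, not as an established loss.

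**What to change.** Before unblinding, amend the Statistical analysis section so that the primary comparison of each primary outcome is a logistic regression with treatment and baseline oxygen index. Report the result as a standardised risk difference with 95% CI, which also suits the plan's use of confidence intervals to judge superiority. Define oxygen index as the trial measures it, since the article gives no definition, and state how a missing baseline value is handled so that no randomised patient drops out of the model. Keep the chi-square or Fisher test as a sensitivity analysis.

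Confirm from the allocation system whether centre was a stratification factor. Add centre only if it was, with small centres pooled, and do not analyse by individual blocks.

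The cost is wording and programming; no extra visit, measurement or patient is needed. The drawbacks are some model dependence and a possible loss of about one power point if the covariate turns out not to be prognostic.

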### Study design

This study is a randomized, double-blind, placebo-controlled exploratory clinical trial. After receiving written informed consent, the subjects who passed the screening criteria will be recruited and randomly divided into the intervention group or the control group at a ratio of 1:1. After 4 weeks of treatment, the patients were followed up for 12 weeks. The study flow chart is summarized in Fig. 1, and the timing of treatment and follow-up are detailed in Table 1.

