### Outcomes

#### Primary outcome

Treatment failure rate: The treatment failure is defined as the symptoms or signs that have not improved or worsened (intubation, treatment with a ventilator, etc.), or the occurrence of new significant symptoms and signs, or new infection, or death. The number of treatment failures in two groups was recorded during the treatment period (4 weeks).All-cause mortality at 16 weeks (end of the follow-up): The number of deaths will be recorded at 16 weeks.

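### Overall survival is defined as a survival time but tested by χ² or Fisher's exact test, which discards timing and repeats the primary 16-week mortality comparison

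*Protocol article*

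**What the plan says.** All references are to the Protocol article.

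- **Secondary outcomes** defines the outcome as "Overall Survival: Survival time up to 16 weeks".
- **Statistical analysis** states "Overall Survival, acute exacerbation rate, and intubation rate will be compared between groups using the" χ² or Fisher's exact test. The only other duration, length of hospitalization, gets a t-test or Wilcoxon test in the same section.
- **Primary outcome** includes "All-cause mortality at 16 weeks (end of the follow-up): The number of deaths will be recorded at 16 weeks".
- **Statistical analysis**, on the primary outcomes: "The primary outcome of this study is treatment failure rate and all-cause mortality rate in each group". It continues "They will be compared between groups using the" χ² or Fisher's exact test.
- **Table 1** schedules all-cause mortality and overall survival at the same visits, day 7 to week 16. Both are analysed in the full analysis set.
- The article names no Kaplan-Meier, log-rank or Cox analysis.
- **Withdrawal, dropout, and discontinuation** lists deterioration, serious adverse events, unwillingness to continue and loss to follow-up. **Participants** names an intention-to-treat analysis for missing data and promises efforts to trace lost patients.

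**The concern.** A survival time and a two-category test do not fit together, and the article does not say how one becomes the other. If overall survival is read as alive or dead at week 16, the comparison is the primary mortality comparison with its columns swapped. A reader of the results would see two mortality findings where there is one.

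The timing of death is lost as well: a death on day 10 and a death on day 110 count the same. The Sample size section says that this trial will supply data for a formal sample size calculation, and the article promises a later trial with longer follow-up. A single proportion at week 16 says little about the survival curve on which such a trial would be planned.

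**Working it through.** The plan gives no power, event count or effect size to reproduce, so the check has three parts.

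**Inputs from the article.** There are "40 participants in the intervention group, and 40 in the control group" (Sample size). On duration, "After 4 weeks of treatment, the patients were followed up for 12 weeks" (Study design), so the horizon is 4 + 12 = 16 weeks = 112 days, or about 3.68 months. The Background gives a median survival of about 3–4 months and an in-hospital mortality of 55–80%.

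**Assumptions not in the article.** Hazard ratio 0.5, exponential survival, two-sided 5% level, and early loss of 0–20%.

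**1. Duplication.** Take 22/40 against 28/40 deaths (18 and 12 survivors).

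χ² = 80 × (22×12 − 18×28)² / (50 × 30 × 40 × 40) = 80 × 240² / 2,400,000 = 1.92, so p = 0.166.

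Swapping the death and survivor columns changes only the sign inside the square, so the result is identical. Fisher's p is 0.248 both ways. For 18/40 against 26/40, χ² p is 0.072 and Fisher's p is 0.115, again both ways.

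**2. Timing.** Take 24/40 deaths in each arm, evenly spaced over weeks 0.2–4 in one arm and weeks 8–15.8 in the other.

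- χ²: p = 1.00.
- Log-rank: p = 0.11. The hazards here are far from proportional, which is where log-rank is weak.
- Mean survival time up to week 16: (24 × 2.1 + 16 × 16)/40 = 7.66 weeks against (24 × 11.9 + 16 × 16)/40 = 13.54 weeks, a difference of 5.88 weeks.

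The planned test cannot see that difference.

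**3. Power.** The median survival in the Background implies 16-week survival of 0.5^(3.68/3) = 0.43 to 0.5^(3.68/4) = 0.53, so mortality of 47–57%. Treated-arm mortality is 1 − (1 − p₀)^0.5. The simulations used 2,000–2,500 runs per row, so each power figure has a standard error of about √(0.25/2,000) = 1 point. Patients lost early were counted as alive in the 2×2 table.

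| Control mortality | Early loss | Log-rank | χ² (uncorrected) |
|---|---|---|---|
| 47% | 0 | 47% | 46% |
| 52% | 0 | 50% | 51% |
| 57% | 0 | 56% | 57% |
| 47% | 15% | 44% | 42% |
| 52% | 15% | 49% | 47% |
| 57% | 15% | 52% | 50% |
| 70% | 0 | 67% | 64% |
| 70% | 20% | 60% | 57% |
| 80% | 0 | 73% | 67% |
| 80% | 20% | 67% | 58% |

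At 47–57% mortality the two tests are within about 2 points of each other. The gain reaches roughly 5–10 points only near 80%.

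Against Fisher's test, at control mortalities of 55–80%, the log-rank gain is larger, about 8–19 points. Much of that is Fisher's conservatism rather than timing: χ² itself beats Fisher by 8.5 points (54.1% against 45.6%) at 55% mortality without loss.

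**The case against.** The strongest reply is that little depends on this. Overall survival is one of several secondary outcomes in an exploratory trial of 80 patients with no formal sample size, and the article itself admits that the sample is small and conclusions will be limited. The primary mortality outcome is binary at a fixed horizon, so χ² or Fisher is legitimate for it, and a redundant secondary test does not damage it. This stands, and it lowers the severity.

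A reader might infer four stronger things that the article does not support.

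- **That the planned test costs substantial power.** That holds only near 80% control mortality. The 80% is the top of an in-hospital range, not a 16-week figure, and it does not match the 47–57% implied by the stated median survival. Patients needing invasive ventilation at entry are also excluded.
- **That any loss to follow-up biases the proportion.** Bias depends on how lost patients are counted and whether loss relates to prognosis. The article gives no loss rate, does not say that lost patients count as alive, and plans active tracing. Most listed withdrawal reasons do not in themselves make vital status unknown.
- **That a survival curve or hazard ratio will never be estimated.** The article condenses a fuller protocol that is not shown. What can be said is that the test it does state does not fit the outcome it defines.
- **That the primary mortality estimator must change too.** Nothing in this mismatch requires that.

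The proposed remedy also has a limit. If follow-up stops at withdrawal for deterioration or a serious adverse event, censoring there is informative, and Kaplan-Meier and Cox estimates are biased as well.

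**Conclusion.** The mismatch is real, and nothing else in the article resolves it. It is a stated method that does not fit a stated outcome, not a detail left to an analysis plan. Read as status at week 16, the overall survival test reproduces the primary mortality test exactly and adds nothing. That reading is inferred, since the article does not say how the time is dichotomised, but no other fits the 16-week limit and the shared visit schedule.

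The gain from correcting it is a valid, non-redundant time-to-event estimate for planning the next trial. It is not power, on the assumptions of a hazard ratio of 0.5 and exponential survival. Severity: should be fixed.

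**What to change.** In Statistical analysis, take overall survival out of the χ²/Fisher sentence. State instead that it will be described by Kaplan-Meier curves and compared by a log-rank test, with a Cox hazard ratio and 95% CI, or restricted mean survival time to day 112 if hazards are not proportional. Censor at day 112, or at the date last known alive if earlier.

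Add that vital status to week 16 will be sought for every randomized patient, including those withdrawn for deterioration or a serious adverse event, so that censoring is not driven by prognosis. Leave the primary 16-week mortality analysis unchanged.

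The cost is one or two sentences. Table 1 already schedules overall survival at every visit from day 7 to week 16, so no patients, visits or procedures are added. The case report form must hold the date of death or last contact, which the definition of the outcome already requires.
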